## Abstract

**Background and aims:**

Cognitive impairment (CI) after stroke is still a neglected consequence compared to other neurological deficits for which rehabilitation pathways are routinely available. Cognitive teleRehabilitation (CTR) represents an emerging approach that has the potential to reduce healthcare costs and potentially reaching many patients. By means of a randomized controlled trial, the aims are to investigate the prevalence of cognitive impairment after stroke and the efficacy of a CTR program in: (a) reducing the risk of CI 6 months after stroke; (b) generalizability of the cognitive training to real life; (c) impact on cognitive performances. In the treated group, feasibility, adherence and appreciation of the CTR will also be evaluated.

**Methods and outcomes:**

The CIPS-TER study is a 2-year prospective, single-blind, randomized clinical trial. One hundred patients with ischemic or hemorrhagic stroke will be enrolled in the study, within 5–21 days after onset, and randomized to treatment or standard care. The CTR program will consist of up to 40 h (8 weeks) of individual treatment based on memory, attention, executive functions, and visuospatial tasks to be autonomously performed with a tablet. The study outcomes will be evaluated at 6-month follow-up visit and will include the diagnosis of cognitive impairment, activities of daily living, quality of life, changes in frailty status and cognitive efficiency.

**Conclusions:**

CIPS-TER study will expand our knowledge on the potential effect of cognitive rehabilitation on future cognitive and functional decline after stroke.

## Background

Stroke is, worldwide, the first cause of disability in adult-older individuals, and the second cause of death and dementia (Leys et al., 2005). Annually, ~16 million of first ever strokes occur in the world, causing 6.3 million deaths (Katan and Luft, 2018; Barbay et al., 2018). Stroke is costly: total cost in Europe is estimated at about €60 billion/year, of which 45% incurred by healthcare systems, 27% for informal care costs, and 22% for loss of productivity (Katan and Luft, 2018; Barbay et al., 2018; Luengo-Fernandez et al., 2020). Future projections suggest an increase in stroke cases, primarily due to the rise in life expectancy (Luengo-Fernandez et al., 2020).

Post-stroke cognitive impairment (PSCI) encompasses all forms of mild to severe cognitive impairment when onset is temporally associated with stroke (El Husseini et al., 2023). The cognitive profile of PSCI is heterogeneous and depends on the type, location, and severity of cerebrovascular lesions. Cognitive hallmarks of stroke-related cognitive impairment include aphasia, neglect, apraxia, and agnosia, and a disconnection syndrome caused by the dysfunction of integrated brain networks and characterized by deficits in information processing speed and executive functions (Shin et al., 2024). Epidemiological data report that ~75% of stroke survivors experience cognitive changes in the acute phase, 47% if we exclude patients with pre-dementia (El Husseini et al., 2023). At a medium-long term cognitive impairment persists in ~50% of patients, a majority fulfilling criteria for mild cognitive disorder (D'Souza et al., 2021). These latter could maximally benefit from cognitive treatment options especially because there are no drug treatments available as today. Cognitive problems after stroke are associated with poor outcomes in terms of recurrence of major vascular events, disability, institutionalization, and death.

Poststroke dementia (PSD) marks the final stage of a spectrum of clinical manifestations of PSCI and refers to all types of dementia following a stroke (Leys et al., 2005; El Husseini et al., 2023). The prevalence of PSD is influenced by the severity of the stroke and the history of recurrent strokes, with PSD occurring less frequently than mild cognitive impairment. Approximately 30% of individuals with a history of stroke develop dementia, with a higher prevalence observed within the first 3 months after stroke compared to 1 year or more later (Leys et al., 2005; El Husseini et al., 2023). Regarding demographic characteristics, studies demonstrate that advancing age and education are key risk factors for PSD (Leys et al., 2005). Additionally, the likelihood of developing PSD is greater in patients who are already dependent before stroke (Leys et al., 2005). Other important factors are neuroimaging features related to pre-existing brain pathologies, independent of index stroke, markers of small vessel diseases, silent infarcts and neurodegenerative markers, such as atrophy and medial-temporal-lobe atrophy (Leys et al., 2005).

Clinical pathways for stroke rehabilitation are inherently influenced by magnitude and heterogeneity of the initial deficits. Severe stroke patients are usually addressed to rehabilitation hospitals where standard programs are primarily devoted to motor, sensory and language deficits. Early cognitive assessment and cognitive rehabilitation are not routinely performed in the acute stroke setting, and there is a lack of an established pathway dedicated to post-stroke cognitive deficits (Suda et al., 2020). Mild stroke patients are frequently discharged at home, thus increasing the risk that persistent cognitive deficits are underdiagnosed and, ultimately, undertreated (Ishiwata et al., 2025). Data on the efficacy of cognitive rehabilitation in both scenarios are needed to identify the characteristics of stroke patients that could maximally benefit of such cognitive interventions. In 2011 a representative group of stroke survivors, carers, and health professionals convened a consensus meeting aimed at compiling the top 10 research priorities of life after stroke, and the most important unsolved question was: “What are the best ways to improve cognition after stroke?” (Pollock et al., 2012, 2014). In line with this, the NICE guidelines for stroke suggest the inclusion of cognitive rehabilitation within rehabilitation pathways, but concluded also that literature does not provide robust evidence about which interventions will be most effective. Despite its social and economic burden is increasingly recognized, cognitive impairment after stroke is still a neglected consequence compared to other neurological deficits for which rehabilitation pathways are generally more available.^1^

At present, cognitive rehabilitation programs remain the most common approach to treat cognitive impairment after stroke. Cognitive rehabilitation stimulates cognitive functions to maximize the patient's degree of autonomy and independence (Viola et al., 2011); it can be provided in a traditional way (face to face, with paper and pencil) or using innovative technology (De cola et al., 2016). In the last decades, advances in Information and Communication Technologies have led to the development of platforms and applications to enable patients' cognitive rehabilitation therapy at home. Telerehabilitation has the potential to provide both individualized rehabilitation treatment and the opportunity of access to rehabilitation services for people who cannot reach the care centers due to logistical and/or functional problems (Lloréns et al., 2015). Standard cognitive rehabilitation has proven to be effective and efficient at improving cognitive performance after stroke. Considering computer-based cognitive training, the results of a meta-analysis by Ye et al. (2022) showed its non-inferiority compared to the traditional method in stroke patients. Emerging evidence indicates that this type of intervention might be effective for individuals with stroke when supervised by an expert and when the program adheres to the neuroplasticity principles (Ye et al., 2022).

Unfortunately, proves on the use of telerehabilitation in stroke patients are based on studies designed to improve motor function rather than cognition. Despite some preliminary evidence to support the effectiveness of computerized cognitive rehabilitation after stroke, high-quality studies focusing on different illness phases, large samples, and various types of intervention software are urgently needed to further improve evidence in this field (Laver et al., 2020).

In recent years, evidence has shown that specific cognitive rehabilitation strategies, especially when structured as goal-oriented training, can significantly improve cognitive outcomes in stroke patients. For instance, a study on subacute stroke patients demonstrated that goal-oriented proprioceptive training not only improved balance, but also stimulated attention functions (Chiaramonte et al., 2024). These findings support the importance of structured, individualized cognitive interventions in the early phases post-stroke.

We present the protocol paper of a randomized control trial aimed at investigating the prevalence of cognitive impairment after stroke and the efficacy of a cognitive telerehabilitation (CTR) program in: (a) reducing the risk of cognitive impairment 6 months after stroke; (b) generalizability of the cognitive training to real life; (c) impact on cognitive performances. In the treated group, feasibility, adherence and appreciation of the CTR will also be evaluated.

## Methods

CIPS-TER is a 2-year prospective, single-blind, randomized clinical trial aimed at assessing the efficacy of telerehabilitation in stroke patients, started soon after the acute phase of stroke. The experimental design of the study is shown in Figure 1.

**Figure 1 F1:**
[figure not shown]
CIPS-TER study experimental design.

The study is carried out at the Stroke Unit of Careggi University Hospital and at General Rehabilitation Unit of IRCCS Don Carlo Gnocchi in Florence, in accordance with the Helsinki Declaration. The study was approved by Local Ethics Committee (25546_spe) and each patient gave a written informed consent.

Patients included in the study were diagnosed with either ischemic or hemorrhagic stroke, regardless of lesion site. Neuroimaging was used to confirm diagnosis.

The study aims at estimating the incidence of post-stroke cognitive impairment in the short and mid-term, and at investigating the efficacy of a CTR program in reducing the risk of CI 6 months after stroke, the generalizability of cognitive training to real life and the impact on cognitive performances. It also aims at evaluating the effect of cognitive training on real-life activities (independence in daily living and quality of life). In the treated group, feasibility, adherence and appreciation of the CTR will also be evaluated.

Inclusion criteria of the study are: ischemic or hemorrhagic stroke (within 5–21 days after onset); age >18 years; evidence of impairment in global cognitive efficiency; NIHSS motor arm item = 0 in at least one arm; fluid Italian speaking; ability and willingness to sign informed consent.

Exclusion criteria are: normal cognitive functioning; pre-existing dementia; severe aphasia; motor deficits in both upper limbs; visual deficits.

All participants diagnosed with ischemic/hemorrhagic stroke are assessed within 5–21 days from onset. Table 1 shows the type of information collected and the instruments applied. Clinical information is retrieved from the clinical records; instruments are administered to patients and caregivers.

**Table 1 T1:** Data collected for screening and baseline evaluation and types of instruments used.

**Study phase**		**Data collection and instruments**
Screening Evaluation	Stroke severity	• NIHSS^*^
	Global cognitive efficiency	• Montreal cognitive assessment (MoCA)^*^ (Nasreddine et al., 2005)
	Verbal comprehension ability	• Token Test in those patients with 1 or 2 at NIHSS language item^*^ (Renzi and Faglioni, 1975)
	Pre-existing cognitive impairment	• Informant questionnaire on cognitive decline in the elderly (IQ-Code)^#^ (Jorm, 2004; van Nieuwkerk et al., 2021)
Baseline Evaluation	Demographics^°^	• Age • Sex • Years of education • Educational degree • Employment status • Profession • Civil status • Living condition
	Vascular risk factors^*^^°^	• Hypertension • Diabetes • Physical Activity • Current smoking habits • Previous smoking habits • Alcohol consumption • Hypercholerestolemia • Hypertriglyceridemia • Atrial fibrillation • Ischemic heart disease • Heart failure • LDL cholesterol assay
	Medical history^°^	• Gait disorders • Thyroid diseases • Migraine/headache • Head injury • Epileptic seizures • Memory disorders • Psychiatric disorders • History of previous stroke
	Home therapy^°^	• Anticoagulants • Antiplatelet agents • Statin
	Secondary prevention therapy adopted in the hospital^°^	• Anticoagulants • Antiplatelet agents • Statin or other treatment
	Neglect	• Star cancellation test^*^ (Halligan and Robertson, 2000; Wilson et al., 1987)
	Apraxia	• Ideomotor apraxia test^*^ (Spinnler and Tognoni, 1987)
	Fragility	• Tilburg frailty indicator (TFI)^*^ (Gobbens and Uchmanowicz, 2021; Mulasso et al., 2016) • Fried criteria (including IPAQ)^*^ (Fried et al., 2001; Mannocci et al., 2010)
	Cognitive reserve	• Cognitive reserve index questionnaire (CRIq)^*^ (Nucci et al., 2012)
	Premorbid functional state	• Activities of daily living (ADL)^#^ (Katz et al., 1963) • Instrumental activities of daily living (IADL)^#^ (Lawton and Brody, 1969) • Modified Rankin scale (mRS)^#^
	Clinical characteristics of index stroke^°^	• Date of stroke • Date of hospitalization • Reason for hospitalization • Lesion type • Pre-stroke mRS • OCSP • TOAST • acute phase treatments • Complications during hospitalization • NIHSS at 24 h • NIHSS at 48 h
	Neuroimaging characteristics of index stroke^°^ Pre-existing brain lesions (Wardlaw et al., 2013; Duering et al., 2023; Scheltens et al., 1992)	• Location • Side • Number of lesions • Leukoencephalopathy • Lacunar infarcts (number, location, side) • Cerebral microbleeds (number, location, side) • Enlarged perivascular spaces (Basal Ganglia, Centrum Semiovale) • Cortical superficial siderosis • Non-lacunar infarcts (number, location, side, vascular territory) • Global cortical atrophy • Mesial temporal atrophy
Discharge Evaluation	Functional state	• Activities of daily living (ADL)^*^ (Katz et al., 1963) • Instrumental activities of daily living (IADL)^*^ (Lawton and Brody, 1969) • Modified Rankin scale (mRS)^*^
	Discharge^°^	• Date of discharge • Discharge destination (home, home with outpatient neurorehabilitation pathway, neurorehabilitation hospital) • NIHSS
	Quality of life	• Stroke adapted sickness impact profile (SA-SIP)^*^ (Buck et al., 2000) • EuroQol scale^*^ (Dorman et al., 1998)
	Mood	• Center for Epidemiologic Studies Depression scale (CES-D)^*^ (Lau et al., 2023)

* Patient interview or evaluation.

° Clinical record.

# Caregiver interview.

For each patient, a caregiver or informant is identified and interviewed to assess the premorbid status. Cognitive premorbid status is evaluated by means of the informant questionnaire on cognitive decline in the elderly (IQ-Code) short form (16 items). IQ-Code explores the changes in daily activities requiring memory and other cognitive abilities observed over the last 10 years. An excellent accuracy of the IQ-CODE for detecting pre-existing dementia in transient ischemic attack and stroke was recently found for an optimal cut-off of >3.48 in a large longitudinal population-based study (Jorm, 2004; van Nieuwkerk et al., 2021). To assess severity of aphasia, we use the language item of the NIHSS according to the following criteria: if the score is 3, the patient is excluded. If the score is 1 or 2, we assess reading capabilities and comprehension. For this latter, we use the Token test (Renzi and Faglioni, 1975), excluding patients with an adjusted score below the 5th centile of the normal population. To be included, patients need to be able to use the tablet autonomously. For this purpose, we exclude patients with severe visual and hearing deficits and those not able to move at least one arm (motor item = 0 in at least 1 arm, not necessarily the dominant one).

Cognitive performances at this stage are assessed by means of Montreal Cognitive Assessment (MoCA). MoCA is a 30-point test recommended by the harmonization standards for the diagnosis and assessment of patients with vascular cognitive impairment, and it covers eight cognitive domains: verbal memory, visuospatial abilities, executive functions, attention, concentration, working memory, language, and orientation to time and place (Nasreddine et al., 2005). The predictive value of MoCA in the acute phase of stroke on the diagnosis of mid-term cognitive impairment is the topic of a previous publication from the proponents (Salvadori et al., 2013). MoCA is a good predictor of mid-term PSCI, independent of other clinical, neurological, and functional characteristics, and a cut-off of 21 is found to have good sensitivity (91%), specificity (76%), positive predictive value (80%), and negative predictive value (89%).

To evaluate cognitive performance, raw scores have been demographically adjusted and converted into an ordinal Five-point scale (equivalent score, ES) using national normative data. Equivalent score is a non-parametric norming method based on percentiles distributions, and scores range varies from 0 to 4: ES = 0 corresponds to an impaired performance (i.e., adjusted score below the outer confidence limit for the 5th centile of the normal population); ES = 1 corresponds to a borderline performance (i.e., adjusted score between the outer and inner confidence limits for the 5th centile of the normal population); and ES = 2–4 represents a normal performance (i.e., adjusted score above the inner confidence limit for the 5th centile of the normal population). When ES methodology is not available, performance was classified according to the reference cut-off, as “normal” when the adjusted score was above the 5th percentile or “abnormal” when the adjusted score was below the 5th percentile in the normal population.

To be included in the study, patients must score ≤ 21 on total MoCA adjusted score (Salvadori et al., 2013) or fail in at least one cognitive domain of MoCA. We consider the inclusion of patients with ES ≤ 1 in at least one cognitive domain according to Aiello et al. (2022).

Through the patient's clinical record, the following information is collected: demographics, medical history, comorbidities, vascular risk factors, home therapy, index stroke clinical and instrumental characteristics (Wardlaw et al., 2013; Duering et al., 2023; Scheltens et al., 1992). A centralized reading of available neuroradiological examinations, such as CT and MRI brain, is performed by an expert vascular neurologist/neuroradiologist.

At baseline, patients undergo a cognitive and mood assessment to investigate: neglect (star cancellation test; Halligan and Robertson, 2000; Wilson et al., 1987), apraxia (ideomotor apraxia test; Spinnler and Tognoni, 1987), fragility [Tilburg Frailty Indicator—TFI (Gobbens and Uchmanowicz, 2021; Mulasso et al., 2016) and Fried criteria (Fried et al., 2001) with IPAQ (Mannocci et al., 2010)] and cognitive reserve (CRI Questionnaire; Nucci et al., 2012). At 7 days after discharge, a telephone interview is conducted to investigate: functional state (ADL, IADL, and mRS; Katz et al., 1963; Lawton and Brody, 1969), quality of life [Stroke adapted sickness impact profile—SA-SIP (Buck et al., 2000) and EuroQol (Dorman et al., 1998)] and mood (CES-D; Lau et al., 2023).

During hospitalization, the caregiver interview involves the investigation of the patient's premorbid functional state (ADL and IADL; Katz et al., 1963; Lawton and Brody, 1969) and the possible presence of cognitive decline before stroke (IQ-Code; Jorm, 2004; van Nieuwkerk et al., 2021).

Stratified block randomization is used to assign participants to the experimental (tele-rehabilitation) or control group (standard care). This method ensures an even distribution of participants across predefined strata and minimizes imbalance in group sizes over time. Participants are stratified based on age, sex, NIHSS and MoCA scores. These variables were selected due to their potential influence on the study outcomes. Blocks of fixed size were generated to ensure that the number of participants in each group remained balanced throughout the enrollment process.

Randomization sequences were created using a computer-based random allocation software by the researchers of the Institute of Neuroscience (Florence) of the Italian National Research Council, who were not involved in participant recruitment or data collection and were in charge of the centralized randomization procedure. To prevent selection bias, randomization sequences are concealed from field workers.

Experimental group: the cognitive telerehabilitation program is based on a medical device, with EU declaration of conformity. The product includes a central workstation, located in the clinic. From the central workstation, an expert psychologist ([name]), follows patients' performances and weekly adapts the difficulty of the tasks according to patients' performances. During the 2-month treatment, patients' compliance to the training sessions will be recorded.

Each patient randomized in the experimental group receives a tablet for the telerehabilitation program. This foresees sessions of telerehabilitation for 60 min per day, for 5 days a week, for a total of 8 weeks (totally making 40 h of individual treatment). Exercises are meant to work on the main cognitive domains: memory, language, attention, executive functions, visual-spatial and praxis skills. The daily treatment session includes 10-min exercises for each of the six cognitive domains.

Control group (standard care): participants are instructed to have a normal lifestyle and receive conventional treatments based on clinical indications provided by their referring physicians.

Two months after enrollment, at the end of the treatment session, a phone interview will be conducted to investigate satisfaction and gratification regarding CTR.

The endpoints of the study are to detect cognitive deficits in acute post-stroke phase and measure the impact these deficits might have on functional autonomy and quality of life of patients 6 months after stroke. The primary outcome will be the diagnosis of cognitive impairment, including mild cognitive impairment (MCI) and dementia according to the DSM-5 criteria for the diagnosis of mild or major neurocognitive disorders, respectively (American Psychiatric Association, 2022). Secondary endpoints will include assessment of functional status in daily life, quality of life, frailty and cognitive efficiency.

As shown in Table 2, the 6-month follow-up includes a neurological assessment with updates of clinical information, neurological exam and functional evaluation (NIHSS and mRS). Cognitive performances will be assessed by means of a comprehensive multidomain neuropsychological battery. The medical doctor and the neuropsychologist who will perform the follow-up visit will be blinded to treatment group.

**Table 2 T2:** Data collected for the 6-month follow-up visit with types of instruments used.

**Cognitive domain**	**Test**
Global Cognitive Efficiency	• Montreal cognitive assessment (MoCA)^*^ (Siciliano et al., 2019) • Tele-global examination of mental state (Tele-GEMS)^#^ (Montemurro et al., 2023)
Verbal and visual memory	• Rey's Auditory Verbal Learning test (RAVLT)—immediate recall^*^ (Carlesimo et al., 1996) • Rey'S Auditory Verbal Learning test (RAVLT)—delayed recall^*^ (Carlesimo et al., 1996) • Short Story test^*^ (Novelli et al., 1986) • Rey-Osterrieth complex figure (ROCF)—delayed recall^*^ (Caffarra et al., 2002a)
Constructional praxis, spatial planning skills and visual-spatial skills	• Rey-Osterrieth complex figure (ROCF)—copy^*^ (Caffarra et al., 2002a)
Attention and Executive Functions	• Trail Making test—part A^*^ (Giovagnoli et al., 1996) • Visual search^*^ (Della Sala et al., 1992) • Symbol Digit Modalities test (SDMT)^*^ (Nocentini et al., 2006) • Color Word Stroop test^*^ (Caffarra et al., 2002b) • Trail Making test—part B^*^ (Giovagnoli et al., 1996)
Language	• Phonemic verbal fluency^*^ (Costa et al., 2014) • Semantic verbal fluency^*^ (Costa et al., 2014) • Token test^*^ (Renzi and Faglioni, 1975)
Premorbid Intelligence	• Brief Intelligence test^*^ (Colombo et al., 2002)
Neglect	• Star Cancellation test^*^ (Halligan and Robertson, 2000; Wilson et al., 1987)
Apraxia	• Ideomotor Apraxia test^*^ (Spinnler and Tognoni, 1987)
Quality of life	• Stroke adapted sickness impact profile (SA-SIP)*^*#^* (Buck et al., 2000) • EuroQol scale*^*#^* (Dorman et al., 1998)
Tone and mood	• Center for Epidemiologic Studies Depression scale (CES-D)*^*#^* (Lau et al., 2023)
Fragility	• Tilburg frailty indicator (TFI)*^*#^* (Gobbens and Uchmanowicz, 2021; Mulasso et al., 2016) • Fried criteria (including IPAQ^#^)^*^ (Fried et al., 2001; Mannocci et al., 2010)
Functional status	• Activities of daily living (ADL)*^*#^* (Katz et al., 1963) • Instrumental activities of daily living (IADL)*^*#^* (Lawton and Brody, 1969) • Modified Rankin scale (mRS)*^*#^*

^*^Patient interview or evaluation based on the in-person visit.

^#^Patient interview based on the telephone interview.

The neuropsychological battery will include test to assess global cognitive efficiency (MoCA alternative version; Siciliano et al., 2019), verbal and visual memory [Rey's Auditory Verbal Learning Test—RAVLT (Carlesimo et al., 1996), the Short Story test (Novelli et al., 1986) and Rey-Osterrieth complex figure Delayed-Recall—ROCF DR (Caffarra et al., 2002a)], constructional praxis, spatial planning skills, visual-spatial skills [ROCF copy (Caffarra et al., 2002a)], attention and executive functions [Trail Making Test (Giovagnoli et al., 1996), Visual Search (Della Sala et al., 1992), Symbol Digit Modalities Test (Nocentini et al., 2006) and Color Word Stroop Test (Caffarra et al., 2002b)], language [phonemic and semantic verbal fluency (Costa et al., 2014)], Premorbid Intelligence—IQ (Brief intelligence test—TIB; Colombo et al., 2002), quality of life [SA-SIP (Buck et al., 2000) and EuroQol scale (Dorman et al., 1998)], mood (CES-D; Lau et al., 2023), frailty [Fried criteria (Fried et al., 2001), with IPAQ (Mannocci et al., 2010) and Tilburg Frailty Indicator—TFI (Gobbens and Uchmanowicz, 2021; Mulasso et al., 2016)] and functional status (ADL and IADL; Katz et al., 1963; Lawton and Brody, 1969). Neglect, apraxia and verbal understanding are investigated with the same tests that are included in the baseline assessment.

The study protocol also includes an extensive telephone interview for all patients at the follow-up. By means of the phone interview data on global cognitive efficiency (Tele-GEMS; Montemurro et al., 2023), quality of life [SA-SIP (Buck et al., 2000) and EuroQol scale (Dorman et al., 1998)], mood (CES-D; Lau et al., 2023), frailty [IPAQ (Mannocci et al., 2010) and Tilburg Frailty Indicator—TFI (Gobbens and Uchmanowicz, 2021; Mulasso et al., 2016)], and functional status (ADL and IADL; Katz et al., 1963; Lawton and Brody, 1969) will be collected.

The diagnosis of major and minor neurocognitive disorder will be based on the available clinical assessment, i.e., patients who are not present at the outpatient visit will be classified based on the telephone interview.

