### Statistical analysis

The sample size was determined a priori based on data reported in previous studies and reviews on cognitive rehabilitation, along with feasibility and logistical considerations. These included the actual flow of stroke patients admitted to Careggi University Hospital and the Intensive Rehabilitation Unit of IRCCS Don Gnocchi during the planned 12-month enrollment period, along with the availability of dedicated spaces, appropriate settings, and personnel.

Yearly, ~400 stroke patients are admitted to the Stroke Unit of Careggi University Hospital, and ~130 patients are referred to the Intensive Rehabilitation Unit of IRCCS Don Gnocchi. Based on an estimated screening pool of ~550 patients during an enrolment period of 12 months, and accounting for an expected frequency of cognitive deficits in 75% of stroke patients during acute phase (enrolment period), as well as a substantial proportion of ineligible patients and refusals, we estimate to enroll ~100 patients. Eligible patients will be randomized in a 1:1 ratio: 50 will be allocated to the experimental group receiving the telerehabilitation program and 50 to the control group receiving standard care. Both groups will be balanced for key demographic and clinical characteristics. This sample size was determined based on pilot studies and a power analysis to ensure a statistical power of 80% to detect significant differences between the two groups assuming a two-sided alpha level of 0.05.

The data management system will include automatized procedures of data analysis. Specifically, independent sample *t*-tests and chi square tests will be used to compare demographics, vascular risk factors, and global cognitive and functional status, and the results will be available in real time during the whole enrollment period. Stratified block randomization will be employed to balance potential prognostic factors—such as age, gender, MoCA scores, and NIHSS scores—across the two groups, minimizing confounding and enhancing internal validity.

At the conclusion of the 6-month follow-up, primary and secondary outcome analyses will be conducted using SPSS version 28. The analysis will focus on three main objectives:

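### Blocks of one fixed size, with arms visible after allocation, let staff who track allocations by stratum foresee some assignments; how many depends on an unstated block size and number of strata

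*Protocol article*

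**What the plan says.** The Methods describe stratified block randomisation: "Participants are stratified based on age, sex, NIHSS and MoCA scores". The next statement on the scheme is "Blocks of fixed size were generated to ensure that the number of participants in each group remained balanced throughout the enrollment process". Sequences were generated by researchers outside recruitment and data collection, who also run the procedure centrally, and "To prevent selection bias, randomization sequences are concealed from field workers".

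After allocation the arms differ visibly. "Each patient randomized in the experimental group receives a tablet for the telerehabilitation program", and a psychologist adapts the tasks weekly from a workstation in the clinic, while controls receive standard care. The trial is called single-blind, and the only blinding described is this: "The medical doctor and the neuropsychologist who will perform the follow-up visit will be blinded to treatment group".

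The Statistical analysis section gives the allocation ratio ("Eligible patients will be randomized in a 1:1 ratio") and the size ("we estimate to enroll ~100 patients"). The article does not state the block size, the categories of the stratification factors, whether the two clinical units share one list per stratum, or whether recruiting staff learn earlier allocations.

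**The concern.** A concealed list protects the next assignment only as long as that assignment cannot be deduced from earlier ones. With a constant block size it sometimes can: once one arm has used its half of the block, every remaining place in the block is forced. The deduction needs the block size, the patient's stratum and the earlier arms in that stratum. Age, sex, NIHSS and MoCA are known to the clinical team before allocation, and the arm is not hidden from treating staff afterwards.

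Enrolment leaves some discretion: a window of 5 to 21 days after onset, eligibility that can rest on one borderline MoCA domain, and a judgement on ability and willingness to consent. If a foreseen arm influenced whether or when a patient was enrolled, the groups could differ at entry. Blinded assessment at 6 months would not correct that, nor would the unadjusted chi-square test planned for cognitive impairment.

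**Working it through.** **The plan's own figure.** The article states no predictability figure, so there is none to reproduce. Its sample-size statement plays no part in this point.

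**Inputs from the article.** 1:1 allocation, about 100 patients, four stratification factors, one fixed block size.

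**Assumptions, because the article is silent.** Each factor is split in two, giving 2 × 2 × 2 × 2 = 16 strata. Patients fall into strata at random with equal probability, so 100/16 = 6.25 per stratum on average. The observer knows the block size and sees all earlier allocations.

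**Step 1: one complete block.** In a 1:1 block of size b, the expected share of forced places is 1/(b/2 + 1). Check at b = 4: of the six possible orders, two (AABB, BBAA) have two forced places and four have one. The mean is (2×2 + 4×1)/6 = 4/3 places, and (4/3)/4 = 33.3% = 1/(2 + 1).

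**Step 2: 100 patients spread over strata.** The last block in each stratum is usually unfinished, and its forced places come at the end, so the share falls. For b = 2 this can be done by hand. The number forced in a stratum of n patients is n/2 rounded down, and n is odd about half the time. The expected number is (6.25 − 0.5)/2 = 2.875 per stratum, and 16 × 2.875 = 46.0 per 100 patients. For the other sizes, the probability that each block position is forced was averaged over the binomial distribution of stratum size. Simulation gave the same results to within about 0.2 percentage points.

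| Fixed block size | Complete blocks | 16 equal strata | 36 equal strata |
|---|---|---|---|
| 2 | 50% | 46% | 41% |
| 4 | 33% | 27% | 18% |
| 6 | 25% | 17% | 5% |
| 8 | 20% | 9% | 1% |
| 10 | 17% | 4% | 0.1% |

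With 16 uneven strata the simulated shares are about 46%, 27%, 18%, 12% and 8%.

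**Step 3: an observer who must infer the size.** Suppose the observer still sees everything but knows only that the size is 2, 4, 6 or 8, each equally likely beforehand. At a true size of 4 in 16 strata, logically certain assignments fall from 27% to about 6%. About 21% can still be predicted with more than 95% probability.

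**Step 4: randomly varied sizes.** The observer knows the set of sizes but not their order; 16 equal strata.

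| Scheme | Certain | Best guess correct |
|---|---|---|
| Fixed 4 | 27% | 68% |
| Varied 4/6 | 5% | 66% |
| Varied 2/4/6 | 3% | 67% |
| Varied 4/6/8 | 2% | 64% |

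Varying the size removes most of the certainty and little of the general predictability.

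**The case against.** Several points on the other side have force.

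- **Who sees the arms.** The article does not say that recruiting staff learn earlier allocations. The tablet and the weekly adaptation make the arm visible to the treating psychologist, who is not said to recruit. This stands as a condition on the point. However, the article describes no separation between recruiting and treating staff.
- **Two units.** Recruitment runs at a stroke unit and a rehabilitation unit, and site is not listed as a stratification factor. If both draw on one list per stratum, staff who see only their own unit cannot locate block ends. A simulation with a 75/25 split (from the article's 400 and 130 patients a year) found no certain assignments at the larger unit for sizes 2, 4 and 6. The risk then returns only if allocations are pooled across units.
- **Limits on selection.** Stratifying by age, NIHSS and MoCA narrows the prognostic differences that could be exploited within a stratum, and the article says that consecutive patients are evaluated. Both reduce the room for selection, but neither removes it.
- **Small gain.** Best-guess success hardly changes, as shown above. Enrolment began in April 2024 with 12 months planned, so few unstarted blocks may remain.

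A reader might infer that between a sixth and nearly a half of assignments can be known in advance. The documents do not support that as an unconditional range. It holds for blocks of 2 to 6 in 16 strata with a fully informed observer, and it is not a lower bound.

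A reader might also put a size on the resulting bias. For example, a 10-point shift in risk in each direction on every certain assignment at size 4 would give 0.27 × 20, or about 5 points. Nothing in the article supports such a shift, so no bias figure is claimed here.

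**Conclusion.** The point holds as a conditional weakness in a stated design choice. The article itself specifies the fixed block size, so this is not a detail lost in condensing a protocol. Concealing the list does not cover deduction from earlier visible allocations. How much is exposed cannot be fixed from the article: the 4% to 46% across block sizes 10 to 2 is a worst case that rests on the assumptions listed above. Nothing in the article shows that selection has occurred or that the primary comparison is biased. The case for acting is that the remedy costs little in a trial whose arms are visible after allocation.

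**What to change.** For blocks not yet started, the central randomisation unit should generate permuted blocks of randomly varied size within each stratum, for example 4 and 6, and keep the sizes undisclosed to both clinical units. Blocks already open should be completed as generated, so that the switch does not cut them short. The Methods sentence on fixed-size blocks should be amended and the date of the switch reported.

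The cost is regenerating the unstarted part of the lists and a short amendment, with no extra patients, visits or staff. Arm sizes become slightly more variable. In simulation over 16 unequal strata, the standard deviation of the difference in arm sizes was about 4.2 patients with sizes 4/6 and 3.8 with 2/4/6, against 3.7 with fixed blocks of 4. The benefit is limited to patients still to be randomised.
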